### Recruitment

It is estimated that four to five new semen analyses are conducted in our andrology unit per day. We will screen the semen analysis result for a patient’s potential eligibility following the TMS criteria. Once identified, our research assistant will contact the patient, explain the study, and invite him to join it. If the patient is interested, the patient will have another semen analysis and blood drawing to confirm his eligibility. Once the patient fulfills our criteria, our reproductive medicine practitioner will further inform him of our project and ask for his consent.

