### Eligibility criteria

#### Inclusion criteria

Patients with less than 20 million total progressive motile sperm will be recruited in this study. Since the TMC is so far the most predictive indicator for achieving pregnancy [4, 5], other seminal parameters such as morphology and other physical properties are not included in the criteria.

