### Interventions

#### TCM WZYZ formula preparations

Traditionally and clinically most Chinese herbal medicines are prepared by decoction in boiling water for hours. In this study, the individual concentrated herbal medicine granules prepared from standardized decoction methods using state-of-the-art concentration technologies according to the Good Manufacturing Practices (GMP) standard will be obtained from PuraPharm® International (H.K.) Ltd. (Hong Kong). The individual concentrated herbal medicine granules will be prepared in sachet form. The modified Wuzi Yanzong pill will be composed of Fructus Lycii 2.4 g, Fructus Rubi 3 g, Semen Cuscutae Chinensis 2.4 g, Semen Plantaginis 2.4 g, and Fructus Schisandrae 2.4 g, plus Radix Rehmanniae Glutinosae Conquitae 3 g, Polygonati Rhizoma 3 g, Cistanches Deserticolae Herba 2 g, Epimedii Herba 2 g, and Cervi Cornus Colla 0.6 g, for a total of 23.2 g divided into two doses per day. For oral administration, the sachets at the designated daily dose are mixed to combine each Chinese medicine. A Certificate for Clinical Trial is not required, as our formula dose package has satisfied the Chinese Medicine Ordinance (Cap. 549 Laws of Hong Kong).

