**Fig. 1 Fig1:**
[figure not shown]
Study flow chart

**Table 1 Tab1:** Schedule of the study process

Time duration Time point	Study period								
	Recruitment by reproductive practitioner	Allocation by TCM team	Post allocation						
	1st visit	0 week	1–6 weeks	2nd visit^a^	7–12 weeks	3rd visit^a^	3–6 months	4th visit^a^	6–12 months
Enrollment:									
Eligibility screen	X								
Informed consent	X								
Allocation		X							
Interventions									
Administration of investigational product			X		X				
Assessments									
Semen analyses		X		X		X		X	
Blood tests		X				X			
Sperm DNA fragmentation		X		X		X		X	
Sperm cryotolerance		X		X		X		X	
Endocrine-disrupting chemicals test		X		X		X		X	
DNA maturity assay		X		X		X		X	
Liver and renal function assessment		X				X			
Natural conception and pregnancy outcome^b^									X

^a^ The 2nd through 4th visits are scheduled at the end of the time duration

^b^ Natural conception and pregnancy outcome are recorded by phone follow-up

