#### Blood tests

Hormone FSH and testosterone will be tested, because the levels of the two hormones are closely related to the testis function. Complete blood picture and liver and renal functions tests will also be included to assess the safety of both the TCM formula and placebo.

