### Randomization and allocation concealment

As consented patients join the study, they will be randomly assigned in two groups (1:1 ratio) using computer-generated random numbers managed by the Integrative Medicine team. The study medications (TCM WZYZ formula and placebo) will be prepared as similar-looking medications, in the same blisters. The placebo will also mimic the herb’s appearance and smell. Our clinicians who are providing care and the patients themselves will be blinded to the type of treatments for the patients. To achieve high accuracy, the trial will follow the updated guidelines from the Consolidated Standards of Reporting Trials (CONSORT) 2010 Statement [12] and the CONSORT for TCM for reporting our parallel group randomized trials [13]. Unblinding should occur only in exceptional circumstances when problems cannot be solved with ongoing randomization. Unblinding should be performed by an authorized investigator. The investigator should report all unblinding events and their reasons on the corresponding case report form (CRF).

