### Quality assurance

A Data Monitoring Committee (DMC) has been established. The DMC is composed of one independent chairman from the Clinical Research Management Office of the Chinese University, one independent member from the Department of Obstetrics and Gynaecology, and one independent member from the School of Chinese Medicine. The responsibilities of the DMC are data monitoring, interim analysis, assessing adverse events and cases with abnormal liver or renal function results after the intervention, reviewing core trial processes and documents, and discussing any amendments to the main study protocol.

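### Blood is said to confirm eligibility, yet no listed criterion uses a blood result, no stated rule covers an abnormal baseline liver or renal test, and the order of consent and blood draw differs between sections

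*Protocol article*

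**What the plan says.** The Recruitment section describes a man found through a screening semen result. If he is interested, "the patient will have another semen analysis and blood drawing to confirm his eligibility". Consent comes next: "Once the patient fulfills our criteria, our reproductive medicine practitioner will further inform him of our project and ask for his consent". The Randomization section then says: "As consented patients join the study, they will be randomly assigned in two groups".

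The criteria themselves are short. The single inclusion criterion is a sperm count: "Patients with less than 20 million total progressive motile sperm will be recruited in this study". The Exclusion criteria section gives four items: known causes or abnormalities of the reproductive organs, azoospermia, known chromosomal abnormalities, and normal WHO values throughout.

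Table 1 puts the eligibility screen and informed consent in the 1st-visit (recruitment) column. The row "Liver and renal function assessment" and the blood tests row are marked in the week 0 column, which is also the allocation column, and again at the 3rd visit.

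The Blood tests section gives these tests a safety purpose: "Complete blood picture and liver and renal functions tests will also be included to assess the safety of both the TCM formula and placebo". Ethical considerations repeats that purpose and places the tests at baseline and at the end of treatment. The only text on what happens to an abnormal result is in the Data Monitoring Committee's remit under Quality assurance: "assessing adverse events and cases with abnormal liver or renal function results after the intervention".

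**The concern.** Two statements in the article do not fit together. A test can confirm eligibility only if some criterion depends on it, and here none does. The man moves on once he meets the criteria, and those criteria are silent on blood. Followed as written, the list admits a man whose baseline liver or renal function is clearly abnormal.

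The order of steps also differs. Recruitment takes blood and then asks for consent; Table 1 shows consent and then blood. Staff following the article cannot do both.

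What is at stake is patient safety and clear conduct, not inference. The product is a ten-component oral formula, taken daily "for a total of 23.2 g divided into two doses per day". The plan already collects the baseline result that would identify a man who perhaps should not start it, but does not say how that result is used.

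**Working it through.** There is no sample-size or power figure to reproduce. The check sets the sections side by side.

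**1. Does any criterion depend on blood?** Inclusion 1 + exclusions 4 = 5 criteria. Those decided by a liver, renal, blood-count or hormone value: 0. The closest is chromosomal abnormality, but it applies only when already known, and no karyotype is among the blood tests named under Study process or Blood tests.

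**2. Where do the tests fall in Table 1?** The nine columns, in order, are: 1st visit, week 0, weeks 1–6, 2nd visit, weeks 7–12, 3rd visit, months 3–6, 4th visit, months 6–12.

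| Row | Columns marked |
|---|---|
| Eligibility screen, informed consent | 1 (1st visit) |
| Allocation | 2 (week 0) |
| Blood tests; liver and renal assessment | 2 (week 0) and 6 (3rd visit) |
| Administration of product | 3 and 5 (weeks 1–6 and 7–12) |

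The baseline test shares a column with allocation, and the table sets no order within that column. Dosing starts one column later.

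**3. When is the next liver or renal test?** The 3rd visit falls at the end of week 12, so the interval is 12 − 0 = 12 weeks = 84 days. Nothing is marked at the 2nd visit (week 6). Study process says blood is taken alongside the semen samples, but describes it as being for hormone levels. Scheduled intake in the active arm over the interval is 23.2 g × 84 = 1,948.8 g. That restates the dosing schedule and is not a measure of risk.

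**4. In what order do consent and blood come?**
- Recruitment: blood draw, then criteria met, then consent. Randomization adds: consented men are allocated.
- Table 1: consent (column 1), then bloods (column 2, with allocation).
- Study process: sperm count, criteria check and consent, then random assignment, with no blood result mentioned in the eligibility step.

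If the Recruitment draw and the week 0 draw are the same, the two orders conflict. If they are separate, the draw said to confirm eligibility is missing from Table 1.

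**5. Who acts on an abnormal result?** The committee's remit covers results after the intervention. Retention says enrolled men receive written feedback of their liver and kidney tests. Neither attaches a consequence to an abnormal baseline value.

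**6. How many men might this involve?** The article gives no prevalence. Purely as an assumption, take 1% to 5%. With the stated total of 286: 286 × 0.01 = 2.9 and 286 × 0.05 = 14.3. The stated 181 per arm gives 2 × 181 = 362 instead: 3.6 and 18.1. So the range is about 3 to 18 men, half of them on placebo under 1:1 allocation. The point does not rest on this range.

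**The case against.** The strongest reply is that this is loose wording in a condensed article. Recruitment mentions only a blood draw, not liver or renal tests, and the bloods may be meant simply as a safety baseline. Laboratory cut-offs and rules for acting on results often sit in the full protocol, which is not shown. Staff see the results, since men receive written feedback on them, and weekly calls record adverse drug reactions. Ethical considerations describes the formula as mild and without known toxicity.

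Much of that stands, and it limits the point. A reader might infer that an abnormal baseline result would not stop a man being randomised and dosed. The documents support only that no stated rule stops him; a practitioner may well do so. A reader might also infer that nothing places the result before allocation. Recruitment and Randomization read together do put the draw before consent and consent before allocation. Table 1 leaves the order within week 0 open, and its 1st-visit and week 0 columns may be one occasion, since the abstract counts four visits in all.

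The condensed-article argument does not remove the point. The article presents its exclusions as a complete list and separately gives blood an eligibility role that this list does not support. If the full protocol holds a liver or renal exclusion, the article states the list wrongly; if not, the gap is real. Nor does the safety-baseline reading help, because under it the baseline result is still tied to no enrolment rule.

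**Conclusion.** The point holds in limited form, at minor to moderate severity. The eligibility role given to blood has no matching criterion (0 of 5), the consent and blood order differs between Recruitment and Table 1, and an abnormal baseline liver or renal result has no stated consequence, with no scheduled retest for 12 weeks.

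This rests on the article as printed. It does not show that men with abnormal results would in fact be dosed, or that anyone would be harmed: neither the intake figure nor the assumed 1% to 5% is evidence of harm. It also does not show that blood is taken without consent in practice. A reader of Recruitment alone might conclude that, but Table 1 puts consent first and Ethical considerations requires permission before recruitment. What the documents show is two stated orders. Power, error rates and the efficacy analysis are not affected.

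**What to change.** Add to the Exclusion criteria a fifth item: clinically significant abnormal baseline liver or renal function, with cut-offs set by the trial's clinicians. Amend Recruitment and Table 1 to give one sequence: consent, then the baseline blood draw, then review of the result, then allocation.

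The tests are already planned for every man, so no new procedure is needed. The costs are a short amendment, a short wait for results before allocation, and the loss of a few men (about 3 to 18 under the assumed 1% to 5%). They would be excluded before randomisation and can be replaced, so the randomised sample size need not change.

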### Randomization and allocation concealment

As consented patients join the study, they will be randomly assigned in two groups (1:1 ratio) using computer-generated random numbers managed by the Integrative Medicine team. The study medications (TCM WZYZ formula and placebo) will be prepared as similar-looking medications, in the same blisters. The placebo will also mimic the herb’s appearance and smell. Our clinicians who are providing care and the patients themselves will be blinded to the type of treatments for the patients. To achieve high accuracy, the trial will follow the updated guidelines from the Consolidated Standards of Reporting Trials (CONSORT) 2010 Statement [12] and the CONSORT for TCM for reporting our parallel group randomized trials [13]. Unblinding should occur only in exceptional circumstances when problems cannot be solved with ongoing randomization. Unblinding should be performed by an authorized investigator. The investigator should report all unblinding events and their reasons on the corresponding case report form (CRF).

### Quality assurance

A Data Monitoring Committee (DMC) has been established. The DMC is composed of one independent chairman from the Clinical Research Management Office of the Chinese University, one independent member from the Department of Obstetrics and Gynaecology, and one independent member from the School of Chinese Medicine. The responsibilities of the DMC are data monitoring, interim analysis, assessing adverse events and cases with abnormal liver or renal function results after the intervention, reviewing core trial processes and documents, and discussing any amendments to the main study protocol.

### Data management

All information regarding the participant will be carefully recorded on the CRF. All errors will be crossed out and corrected and signed by the corresponding investigator. The study data in the CRF will be entered and coded to a corresponding e-CRF by the double-entry method.

Hard copy CRFs are stored in a separated room and locked in filing cabinets. Only authorized investigators are permitted to access this information. The e-CRFs are stored in a server encrypted using the Advanced Encryption Standard, and only authorized investigators are permitted to access them. The researchers will ensure the confidentiality of sensitive data by minimizing the number of personnel who handle subject data.

### Data analysis

All the data are reported as percentages for nominal data or means ± standard deviation (SD) for continuous data. Patients with less than 70% compliance (i.e., out of 90 days treatment taking the WZYZ formula, less than 63 days of treatment completed) will be excluded. They will be considered as having dropped out and will not be included in the final analysis, but will be included in the intention-totreat analysis. The compliance will be checked by our research staff based on the patient diary and phone calls every 2 weeks. For non-compliance and missing outcomes, we will use two sets of analyses. The full analysis set (FAS) will include all patients who are randomized and will be conducted according to the intention-to-treat principle. The per protocol set will include all patients of the FAS who complete follow-up and do not have serious protocol violations.

For the baseline comparison, the independent Student *t* test or the Mann-Whitney *U* test is used to evaluate the mean or median differences between the placebo and intervention groups for continuous data depending on whether the data are normally distributed, and the chi-squared test is used for frequency comparison. For longitudinal data with a baseline, we will use repeated measures analysis of covariance (ANCOVA) to evaluate the mean difference between and within groups. All the tests are two-tailed, and the significance level is defined as a value of < 0.05.

### Ethical considerations

Ethical approval of the protocol and informed consent forms has been granted from the Clinical Research Ethics Committee (CREC), CREC Reference number 2016.617-T (Additional file 1).

All subjects will be given a detailed explanation of the trial, and their permission will be obtained before they are recruited into the study. A written consent form will be signed by the patient see (Additional files 2 and 3). Semen analysis is a direct and non-invasive method for semen quality evaluation. The TCM remedy is a mild formula with no observable side effects and no known toxicity. We have included liver and renal function tests for each patient at the baseline and at the completion of the WZYZ treatment to assess the safety of the TCM remedy. Blood sample taking will cause extremely mild irritation to the skin, and the infection risk is low.

This study is in compliance with the Declaration of Helsinki and the Guideline for Good Clinical Practice of the International Conference on Harmonisation.

## Discussion

One out of six couples encounters subfertility problems worldwide, and male infertility contributes to half of the cases. Regardless of the cause, there is no effective therapeutic agent available to reverse poor semen quality. Thus, there is an urgent need to explore a potent therapeutic regimen for male fertility. The Wuzi Yanzong formula is a traditional Chinese formula that is effective in improving male sperm quality, but a solid RCT to support this is lacking. This RCT will be conducted by a group of experienced experts from different fields, as the prerequisite to run this project is a group of experts from reproductive medicine, Chinese medicine, and endocrinologists. With our experience in conducting RCTs, this project will demonstrate the compelling clinical effectiveness of the Wuzi Yanzong formula, with the hope that it will lead to the first promising RCT-proven regimen on curing male infertility.

### Trial status

This trial is at Version 1.3, 16/10/2018 (ChiTR). The actual study start date was 27/02/2018; the anticipated study end date is 31/01/2022. The recruitment start date was 27/02/2018; the anticipated recruitment end date is 31/01/2020.

## Data Availability

Not applicable.

## Abbreviations

ART: Assisted reproductive technology
CONSORT: Consolidated Standards of Reporting Trials
CREC: Clinical Research Ethics Committee
CRF: Case report form
DMC: Data Monitoring Committee
FAS: Full analysis set
FSH: Follicle-stimulating hormone
GMP: Good Manufacturing Practices
RCT: Randomized controlled trial
TCM: Traditional Chinese medicine
TMS: Total motile sperm
WHO: World Health Organization
WZYZ: Wuzi Yanzong
